### 2.13. Dissemination Plans

The results will be published in the form of articles in peer-reviewed scientific journals. There are no publication restrictions resulting from funding. After all results are published, the anonymized data will be available on demand. Moreover, a website will be developed to provide information about the project and the current status of the results to the interested public.

## 3. Discussion

This study protocol presents a non-randomized, open-label, single-arm trial investigating the feasibility of implementing a mentalization-based integrative team approach (MB-TA) aimed at reducing the risk of maltreatment among hard-to-reach parents in an already existing welfare system. On the basis of convincing evidence that mentalization-based approaches help professionals feel empowered and more confident in working with hard-to-reach patients or clients [15], the present approach focuses on strengthening the competencies of the primary care system so that the risk of maltreatment in burdened families can be reduced. The sample to be surveyed should meet the risk factors for child endangerment since the typical clientele of the EPP shows a high burden (low SES, mental disorder diagnosis, extreme parental stresses, and overload). Additionally, before proposing this study, sixty-nine percent of the EPP clients stay in treatment for less than three months, indicating major problems for the continuity of support [33]. This study’s inclusion criteria will additionally ensure that participating parents have at least one risk factor associated with an increased risk for child maltreatment [2,6,10,11,29]. However, the exact potential for child endangerment in the sample cannot be determined at this time. Self-report questionnaires will be used to measure whether parental risk factors can be reduced through EPP assistance. Self-report measures can be biased but allow data to be collected from a large number of individuals. Moreover, there are hardly any objective measures for the variables collected in this study. For example, parents’ own experiences of abuse can only be requested retrospectively. Less parental stress is significantly associated with fewer inadequate parenting behaviors, as well as child maltreatment [6], which is why the PSI score was chosen as the primary outcome. Actual maltreatment reported by the EPP is used as a secondary outcome since no objective data on this were available before the intervention, and therefore, no pre-post effects can be examined. To our knowledge, the study represents the only feasibility study investigating the effects of mentalization-based psychiatric/psychotherapeutic supervision on childrearing practices and the risk of maltreatment to date. Consequently, the present study gives profound consideration to the repeatedly formulated necessity to develop effective intervention approaches to reduce child maltreatment by empowering the care system. There is a specific need to implement and evaluate intervention approaches within existing welfare systems that meet specific criteria for quality of service, including multi-professional teams, cooperation with community health and welfare services, and work via home visits since these criteria have already been identified as necessary for treatment success [1,8,28]. However, early support by itself seems ineffective at reducing the risk of child maltreatment [24]. It seems of major relevance for staff workers to pay special attention to the known parental risk factors to reduce child maltreatment. At this point, however, EPP staff reports a lack of knowledge. Thus, a team-based approach providing the staff with special knowledge and skills is urgently needed to strengthen the competencies of EPP staff and, thereby, the chance to provide continuous care for burdened families [59]. Mentalization-based intervention programs have emerged in working with hard-to-reach clients since adequate mentalizing allows us to interact in a highly adaptive manner and to take the needs of others into account. One study showed that it allows healthcare professionals to acquire empathy and understanding for their clients and increases consistency in their teamwork [26]. Therefore, the MB-TA seems very promising to support EPP staff and enhance networking between agencies. If the current metalization-based intervention program is feasible, then the effectiveness of the approach should be verified with the help of randomized controlled studies. In case of a confirmatory result, the findings will have important implications for community service and clinical work. The MB-TA can be widely integrated into existing welfare systems. This offers the advantage of a comparatively easy and time-saving implementation process. There is no need to set up a new team of helpers, and existing team structures do not have to be restructured and can simply be supplemented with MB-TA team training and subsequent regular mentalization-based supervision. However, we are currently unable to estimate the exact costs of the intervention. However, the data on cost-benefit analyses show that the consequences of child maltreatment are considerable. A comparison shows that the prevention costs are comparatively minimal compared to the consequential costs of child endangerment. To be more precise, in the area of early intervention, the costs of unprevented child abuse are 60 (moderately calculated) to 159 (pessimistically calculated) times higher than the costs of EPPs. So even if the MB-TA intervention causes higher costs than treatment as usual, it should be cost-effective if there is evidence of its higher effectiveness [60]. In addition to the cost-benefit analysis of German EPPs, Finnish researchers have examined the economic aspects of team supervision and were able to show that team supervision was efficient in this respect [61].

## 4. Conclusions

Children of parents with severe psychosocial risk factors, such as low education levels, low family income levels, social isolation, high levels of parenting stress, mental illness, and a history of early abuse, are prone to maltreatment and neglect. Although home visiting programs have generally shown small but significant overall effects on the prevention of child maltreatment, at-risk families with severe strain do not seem to benefit sufficiently from this support. A crucial factor for success seems to be the quality of the service system, especially supervision and training, which emerged as important implementation factors. In particular, the inclusion of a reflective supervision component resulted in greater program effectiveness. The presented study, therefore, aims to contribute to the further improvement of EPPs by adding mentalization-based team supervision to the already existing welfare service of the German EPP. We hypothesize that mentalization-based supervision supports the staff in developing a more empathetic and consistent approach to challenging clients and a better understanding of parental mental states to keep the families in the care program, thus reducing the risk of childhood abuse, maltreatment, and neglect. Initial experiences with mentalization-based supervision have already shown a high level of satisfaction among EPP staff. In the evaluations that have been carried out to date, employees have also stated that they benefit from the supervision service. Finally, if feasibility emerges from this study, the MB-TA approach can then be incorporated into future intensive evaluation and, with corresponding proof of effectiveness, sustainably improve the EPP in Germany.

## Figures and Tables

**Figure 1 children-11-00267-f001:**
[figure not shown]
Study Flow Chart.

**Table 1 children-11-00267-t001:** Inclusion and exclusion criteria.

Inclusion Criteria	
Parent/caregiver	Must be supported by the EPP Score > 4 on at least one of the five subscales of the Adult Adolescent Parenting Inventory (AAPI version 2.1) Or the presence of socioeconomic disadvantage Or the presence of parental risk characteristics Or teenage motherhood Written informed consent provided by the caregiver
Child	<24 months of age
Exclusion criteria	None

**Table 2 children-11-00267-t002:** Plans for the assessment and collection of outcome data.

Diagnostic Tools	Subject	T0	T1	T2
Sociodemographic data	Parent	X		X
MINI DIPS	Parent	X		
IPDE	Parent	X		
CECA-Q	Parent	X		
AAPI-2 (Version A)	Parent	X		X
AAPI-2 (Version B)	Parent		X	
Infant Care Index	Parent	X		X
PHQ	Parent	X	X	X
PSI	Parent	X	X	X
CAPI	Parent	X	X	X
PRFQ	Parent	X	X	X
F-Sozu	Parent	X		X
BITSEA	Parent			X
IBQ				X
PWIS	EPP staff		X	
Visit log	EPP staff		X	
AMBIT	EPP staff	3 times during the course of the study		
TICS	EPP staff	3 times during the course of the study		
Subgroup:				
Saliva (Epigenetic)	Participant	X		
CTQ	Participant	X		
KERF (MACE)	Participant	X		

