## Abstract

Although home visiting programs have generally shown small overall effects on the prevention of child maltreatment, at-risk families with severe strain do not seem to benefit sufficiently from this support. A crucial factor for success seems to be the quality of the service system. The aim of the current study is to evaluate the effects of mentalization-based team supervision on the already existing welfare service of a German early prevention program (EPP). This will be a non-randomized, open-label, single-arm feasibility study. The EPP staff will be trained according to the mentalization-based team approach (MB-TA) and regularly receive MFT supervision by a trained and experienced child and adolescent psychiatrist. A minimum of eighty-four families with defined risk factors with children below 24 months of age and pregnant women in the third trimester will be included. Assessments will take place at T0 (after inclusion in the study), at T1 (after family care ends, as an intermediate assessment,) and at T2 (as a follow-up). We hypothesize that the risk of maltreatment can be reduced by strengthening the skills and capacities of the primary care system. This will be evaluated at the end of the follow-up period by comparing the Parental Stress Index (PSI) scores of all participants pre- and postintervention. Stress levels and mentalization abilities will be assessed as feasibility endpoints for the participating EPP teams.

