### 2.6. Outcomes

The primary outcome variable is the change in the parent-reported Parental Stress Inventory (PSI, [36]) scores from pre- to postintervention. A high parental burden can be considered a risk factor for dysfunctional parenting behavior. The PSI is a well-established 48-item self-report questionnaire for caretakers and can be utilized as a screening tool for dysfunctional parent–child interactions [37]. Good psychometric properties have been reported for the EBI, with reliability scores ranging from α = 0.95 for the total score to α = 0.93/0.91 for the domain scores. The validity of the instrument has been examined in several studies that have reported substantial associations between EBI scores and various indicators of parental stress [37].

As secondary outcomes, more detailed assessments of the parent and children’s health, as well as parent–child interactions, will be conducted when the child is aged 12, 18, 24, or 30 months. Secondary parental outcomes are the total and subscale scores of the Adult & Adolescent Parenting Inventory (AAPI-2, [38]), parental health (Patient Health Questionnaire, PHQ, [39]), child abuse potential (Child Abuse Potential, CAPI, [40]) and the level of social support (Social Support Questionnaire, Fsozu, [41]). The internal consistency of the depression scale of the German PHQ is given as α = 0.88 [42]. The internal consistencies of the main scales and the total score of the FSozu are between α = 0.81 and α = 0.93 [41]. The reflective functioning of the parents will also be recorded before (T0) and after (T1) the intervention as well as during the follow-up (T2) using the Parental Reflective Functioning Questionnaire (PRFQ, [43]). Estimates of internal consistency were 0.70, 0.82, and 0.75 for the three subscales [43].

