### 2.12. Statistical Methods for Primary and Secondary Outcomes

The effects of the “EPP-plus” are assessed in a pre-post comparison using the PSI scores with a one-sample t-test with a two-sided significance level of 5%. The primary analysis is based on the intention-to-treat (ITT) principle, which aims to include all subjects enrolled in the feasibility study. The analysis of the secondary results is carried out analogously. Exploratory analyses will investigate which family-level risk factors are associated with the magnitude of change in PSI, using linear models and considering the presence of socioeconomic disadvantage (e.g., unemployment, overall socioeconomic status), mental risk characteristics (e.g., mental/physical health, domestic violence), teenage motherhood, immigrant status, parental ELM (assessed by CECA-Q), AAPI-2 pre-intervention total score, age and gender (of parent and child), and child responsiveness (Infant Care Index).

The feasibility of the “EPP-plus” approach will be analyzed descriptively, using frequencies and proportions for nominal or ordinal variables or medians and interquartile ranges for quantitative variables. For feasibility, we will consider the median number of visits per family, the number of supervision sessions, and attendance by the EPP staff to supervision sessions. In addition, acceptance of the “EPP-plus” approach by the staff members and their work-related stress levels will be analyzed at the start, midterm, and end of the trial by linear mixed models accounting for the clustering of team members. Furthermore, potential staff- and team-related factors contributing to the outcome of the “EPP-plus” approach (such as job experience, professional background, etc.) will be analyzed.

All safety data, including adverse events, are analyzed descriptively in the Safety Population (SP), which includes all families who were visited at least once by a team member of the “EPP-plus” team.

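### AAPI-2 is both an entry criterion and an uncontrolled pre-post outcome, so its change may partly be regression to the mean in families who entered by AAPI alone

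*Protocol article*

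**What the plan says.** Table 1 of the protocol article lists as one entry route a "Score > 4 on at least one of the five subscales of the Adult Adolescent Parenting Inventory". It continues with three alternatives: "Or the presence of socioeconomic disadvantage Or the presence of parental risk characteristics Or teenage motherhood". A family supported by the early prevention program (EPP) can therefore enter by any one of four routes, and three of them need no AAPI score.

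The same instrument is an outcome. Section 2.6 states: "Secondary parental outcomes are the total and subscale scores of the Adult & Adolescent Parenting Inventory". Section 2.12 specifies a one-sample t-test at the two-sided 5% level for the pre-post change in PSI and adds: "The analysis of the secondary results is carried out analogously". Section 2.2 describes a single-arm design.

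Table 2 schedules AAPI-2 form A at T0 and T2 and form B at T1. It lists no other AAPI before the intervention. Section 2.12 also uses the "AAPI-2 pre-intervention total score" as a covariate in exploratory models. On timing, the Abstract says: "Assessments will take place at T0 (after inclusion in the study"; Section 2.7 places T0 shortly after the parent agrees to take part.

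**The concern.** When people are admitted because a noisy score lies beyond a threshold, and that score is also the baseline, part of the excess is measurement error that will not recur. The next measurement then tends to lie nearer the mean with no intervention effect at all. Taking any one of five subscales as sufficient gives measurement error five chances to bring a family over the line. A control arm would show the same drift and cancel it, but this trial has none, and the article does not mention regression to the mean.

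An AAPI-2 change of this kind could be read as a change in parenting attitudes due to EPP-plus. It could also enter the effect estimates for the cluster-randomized trial to which Section 2.2 says this study is a first step.

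**Working it through.** **The plan's own figure.** Section 2.8 gives 67 evaluable parents for 80% power at d = 0.35 (one-sample t-test, two-sided 0.05) and 84 recruited with 20% loss. The noncentral t gives power 0.806 at n = 67 and 0.7999 at n = 66, and 67 / 0.80 = 83.75, so 84. Both figures reproduce. They concern PSI and are not affected by this point; n = 67 is used below.

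**Assumptions not in the document.** Five standardized subscales, retest correlation 0.7, inter-subscale correlation 0.3, no true change, the T0 score used for entry, and other risk factors independent of AAPI. The cut-off lies 0, 0.5 or 1 SD above the mean.

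**Everyone enters by AAPI.** Let S be the sum of the five subscales.
- Var(S) = 5 + 20 × 0.3 = 11.
- Cov(S at T0, S at T2) = 5 × 0.7 + 20 × 0.3 = 9.5.
- Expected change = −(1 − 9.5/11) × E[S at T0 | admitted] = −0.136 × E[S at T0 | admitted].
- Simulation gives the mean T0 subscale score among those admitted as 0.119, 0.265 and 0.469 SD for the three cut-offs. Multiplied by 5, E[S] is 0.60, 1.33 and 2.34.
- The expected change in S is therefore −0.081, −0.181 and −0.320.
- The SD of the change is about 1.70 to 1.72, so the spurious standardized change d is about 0.05, 0.11 and 0.19.
- With noncentrality d × √67, the test rejects in about 7%, 14% and 32–33%, against a nominal 5%.

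**Other routes dilute this.** Let q be the share with another qualifying factor and P the chance that any subscale passes (0.896, 0.724 and 0.478 for the three cut-offs). Families with another factor enter whatever their AAPI score, so they carry no selection on it.
- AAPI-only share among those admitted = P(1 − q) / [q + P(1 − q)].
- For q = 0.5 this is 0.47, 0.42 and 0.32; for q = 0.8 it is 0.18, 0.15 and 0.11.
- The spurious d falls roughly in proportion to this share.

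| Share with another factor | cut-off 0 SD | 0.5 SD | 1 SD |
|---|---|---|---|
| none | 7% | 14% | 32% |
| 50% | 5.5% | 6.7% | 8.0% |
| 80% | 5.1% | 5.3% | 5.4% |

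Repeat simulations, and a different reading of the 0.3 (observed or true scores), move the first row by one or two percentage points and the others by a few tenths. At q = 0.8 the spurious d is at most 0.02. A test on a single subscale is less affected: about 10% rejection at the 1 SD cut-off if all enter by AAPI.

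**Sensitivity.** With retest correlation 0.6 to 0.8 and inter-correlation 0.4:
- If all enter by AAPI, rejection is 34% to 61% when 10% of parents pass any one subscale, 11% to 17% when 30% pass, and 5% to 7% when 50% to 70% pass.
- If half have another factor, it is at most 8.5%.
- If 80% do, it is about 5%.

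**A separate earlier AAPI.** If eligibility rests on an earlier administration and T0 is a re-measurement, the simulated artefact in the T0-to-T2 change is zero to within simulation error.

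**The case against.** The strongest objection is that the article never says the T0 score decides eligibility. The Abstract puts T0 after inclusion, Section 2.6 speaks of families being screened and then included, Table 1 names AAPI version 2.1 where other places say AAPI-2, and Table 2 is a plan for outcome data that need not list screening. A reader might infer from Table 2 that the T0 score is documented as the qualifying score. It is not. T0 remains the only pre-intervention AAPI-2 listed, and inclusion can mean consent, so the inference is fair but conditional.

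Second, AAPI is one of four alternatives. Section 2.4 says all families seeking support are included consecutively, and the Discussion describes the typical clientele as heavily burdened, with low SES and mental disorder. The AAPI-only share may well be small, and the table above shows the artefact then nearly vanishes. This stands and limits the size.

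Third, a reader might quote the shift in just those subscales that exceeded the cut-off, which under these assumptions is 0.24 to 0.46 SD. No planned test uses that quantity: the plan tests each subscale and the total across all families.

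Fourth, handling of a secondary outcome is often left to an analysis plan, which is not shown, and the Discussion defers effectiveness to randomized studies. This lowers the priority. But the entry rule, the outcome and the type of test are all fixed in the article itself.

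**Conclusion.** The point holds in conditional form. AAPI-2 is an entry threshold and an uncontrolled pre-post outcome. If T0 is the qualifying score, AAPI-2 change may partly be regression to the mean among families who entered by AAPI alone.

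The false-positive rate of the total-score test ranges from about 5%, when 80% of families have another risk factor, to about 32%, when all enter by AAPI with the cut-off 1 SD above the mean. It goes higher if the cut-off is more extreme. These figures rest on the assumed correlations and on other risk factors being independent of AAPI. The two quantities that decide the matter, the AAPI-only share and the position of the cut-off, are not given.

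Two stronger readings are not supported. One is that some part of any AAPI-2 change must be artefact: the shift runs only back from the selected side, cannot explain movement the other way, and may be close to zero. The other is that the main result is affected: PSI has no entry threshold, so this mechanism does not act on it directly. The point is minor, but inexpensive to settle.

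**What to change.** Keep the AAPI-2 analysis in all enrolled families, in line with the intention-to-treat aim in Section 2.12, and add the following:

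- State which AAPI administration decides eligibility. If it is a separate earlier one, saying so largely settles the point.
- Report the share of families entering by each route, including by AAPI alone.
- Repeat the AAPI-2 change test in families who meet another inclusion criterion (disadvantage, parental risk characteristics or teenage motherhood), and claim an AAPI-2 change only if it holds there.
- Show AAPI-only families separately and descriptively.

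The repeat test works because those families would have entered whatever their AAPI score. It removes only this selection; other sources of drift in an uncontrolled pre-post comparison remain.

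The cost is some wording and a smaller sample in the repeat test. If 11% of 67 families are AAPI-only, 67 × 0.89 ≈ 60 remain; if 32% are, 67 × 0.68 ≈ 46 remain. The loss is sizeable only where the correction also matters more. No new assessment is needed to identify these families: Section 2.12 already uses socioeconomic disadvantage, mental risk characteristics and teenage motherhood in its exploratory models. The article does not say that the qualifying route itself is recorded, so this should be confirmed.

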## Data Availability

Not applicable.
